**We therefore propose the following Specific Aims:**

Specific Aim No.1: To examine the acute response to a sulfonylurea challenge (glipizide 5 mg orally) in subjects at risk of diabetes or with early diabetes (on diet treatment alone), depending on genotype at *KCNJ11* E23K, *TCF7L2* rs7903146, or newly discovered variants linked to type 2 diabetes via associations with related phenotypes, individually or in aggregate

- We hypothesize that subjects with a subset of variants will have an attenuated response, whereas those with a different subset will have no discernible impact on this response

Specific Aim No. 2: To examine the acute response to short-term metformin treatment on the insulin sensitivity index in the same group, depending on genotype at *KCNJ11* E23K, or newly discovered variants linked to type 2 diabetes via associations with related phenotypes, individually or in aggregate

- We hypothesize that subjects with a subset of variants will have a diminished improvement in insulin sensitivity compared to non-carriers

Specific Aim No. 3: To examine acute insulin secretion (by the insulinogenic index derived from an OGTT), GLP-1 and glucacon levels, and metabolomic profiling after short-term metformin treatment (500 mg bid x 4 doses) in the same group of subjects, depending on genotype at *TCF7L2* rs7903146, or newly discovered variants linked to type 2 diabetes via associations with related phenotypes, individually or in aggregate

- We hypothesize that subjects with the risk TT genotype at *TCF7L2* rs7903146, or a subset of variants will have a reduced insulinogenic index and GLP-1 levels than non-carriers

***If successful, this proposal should help clarify the pathophysiologic mechanisms by which these key genetic variants increase risk of type 2 diabetes, and assess their impact on commonly used antidiabetic treatments. In addition, this pilot study will lay the groundwork for a long-term, outcomes-based pharmacogenetic clinical trial.***

# Subject Selection

***III.1. Available samples***

**Our goal is to recruit research subjects likely to require antidiabetic medications in their lifetime.** These include individuals with early type 2 diabetes (on diet treatment alone), or at higher-than-average risk of developing diabetes (impaired fasting glucose, IGT, a history of gestational diabetes, or suffering from the metabolic syndrome, obesity and/or the polycystic ovary syndrome [PCOS]). We have assembled a local team of collaborators with a shared interest in diabetes and metabolic traits, who have ready access to suitable research subjects.

**Our main target for recruitment will be the local Partners Network practices.** Making use of the electronic medical record available to all 12 MGH-based primary care practices, [name] has compiled a Practice-Based Research Network (PBRN), based on the approximately 90,000 primary care patients with regular care at MGH (i.e. an identified MGH primary care physician *and* a clinic visit in the prior 2 years). This database includes a cohort of 7,692 patients with type 2 diabetes seen between 07/01/04 and 06/30/05. Of those, there were 1,547 patients (20.1%) not on glycemic medication therapy (i.e. diet/lifestyle); their characteristics are shown in Table 1.

| Table 1: Demographic characteristics of diet-treated MGH patients with diabetes | |
| --- | --- |
| Female | 775 (50.1%) |
| Age (years) | 65.3 ± 14.7 |
| Caucasian | 1,202 (77.7%) |
| Current smoker | 230 (14.9%) |
| Coronary artery disease | 382 (24.7%) |
| BMI (kg/m^2^) | 31 ± 7.6 |
| N medications | 7.9 ± 5.2 |
| Clinic visits previous year | 7.6 ± 6.2 |
| HbA_1C_ (%) | 6.7 ± 1.1 |
| Mean blood pressure (mm Hg) | 130/74 |
| LDL cholesterol (mg/dl) | 93.7 ± 32.5 |
| Variables are expressed as n (%) or mean ± SD. | |

**A second possible source of volunteers will be non-diabetic subjects with at least one elevated random glucose (>200 mg/dl).** In addition to the above diet-treated patients with diabetes, [name] has identified another ~1,500 MGH primary care patients who do not carry the diagnosis of diabetes, but have at least one random glucose >200 mg/dl in the medical record. Because hyperglycemia is predictive of future diabetes ([78](#_ENREF_78); [79](#_ENREF_79)), this group is at higher-than-average risk of ever requiring antidiabetic drugs.

**Other Partners and Joslin collaborators work with susceptible patient populations.** [name] at the MGH Reproductive Endocrine Unit is currently carrying out a study with about 500 patients with PCOS, only a small fraction of whom (~10%) are on current metformin treatment. Drs. [name] and [name] have an established research program on the metabolic syndrome which comprises approximately 100 subjects with and without HIV infection. [name] has been following a cohort of ~200 women with a history of gestational diabetes mellitus (GDM) ([80](#_ENREF_80)). Finally, we have access to 1,004 non-diabetic subjects formerly enrolled in a Partners-Roche Consortium who have consented to diabetes-related genetic investigation, 25% of whom have BMI >30 kg/m^2^. These cohorts can be further expanded, if necessary, with additional help from the MGH and Brigham Obesity Clinics. At the Joslin Diabetes Center, family members of the diabetic patients will also be recruited.

As the study aims to test the effect of specific genetic variants on pharmacological response, recruitment efforts will also include queries within an institutional biorepository containing samples adequate for genotyping and demographic information on individuals interested in participating in clinical trials. Individuals who have already indicated interest in participating in future studies and given consent for genotype-directed call back into future research studies will be contacted first by mail to assess their interest in participating in SUGARMGH and then, unless otherwise indicated, by phone.

In the event that an individual does not qualify to participate in the study, we will ask if they would like to be contacted by collaborators involved in other research studies.

In the event that recruitment lags, we will advertise outside of the Partners and Joslin networks. This may include posting flyers, internet advertising, newspaper ads and any other forms of displaying the approved flyer.

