***III.2. Eligibility criteria***

**As stated above, we intend to enroll research subjects at higher-than-average risk of requiring antidiabetic medications in their lifetime.** Keeping in mind the possible side effects of the study drugs (glipizide and metformin), we will adhere to the following inclusion and exclusion criteria:

Inclusion criteria:

- Male or non-pregnant female > 18 years of age
- We will target preferentially people at risk of diabetes or requiring diabetes meds
  - The first tier of risk will be illustrated by one of the following variables (e.g. established type 2 diabetes on diet therapy alone, elevated random glucose in electronic medical record, PCOS, metabolic syndrome, obesity, history of gestational diabetes, etc.)
  - The second tier of risk will be illustrated by other features that correlate with diabetes risk, such as a history of hypertension or dyslipidemia
- Otherwise healthy subjects may also be candidates for the study.
- Able and willing to give consent relevant to genetic investigation

Exclusion criteria:

- Pregnant, nursing or at risk of becoming pregnant
- Currently taking any medications for the treatment of diabetes
- Currently on metformin for any other indication (e.g. PCOS)
- Onset of diabetes before age 25, with autosomal transmission of diabetes across three generations
- History of liver or kidney disease
- Known severe allergic reactions to sulfonamides
- History of porphyria
- Documented estimated glomerular filtration rate (GFR) < 60 ml/min/1.73 m^2^, based on the most recent serum creatinine measurement available in the electronic medical record, and calculated by the Modification of Diet in Renal Disease equation ([81](#_ENREF_81)) available at <http://www.nephron.com/cgi-bin/MDRD_GFR.cgi>
- Currently taking medications known to affect glycemic parameters, such as glucocorticoids, growth hormone or fluoroquinolones
- Planned radiologic or angiographic study requiring contrast within one week of completion of this study
- Established coronary artery disease (CAD), defined as:
  1. History of myocardial infarction.
  2. History of revascularization (coronary artery bypass grafting, percutaneous coronary intervention (e.g. stenting or balloon angioplasty).
  3. Evidence of ischemia on cardiac stress test.
- Enrolled in any other interventional study at time of screening through completion of study protocol
- History of bariatric surgery
- History of seizures
- History of stroke/CVA

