***VI.2. Statistical analysis***

**Non-normal variables will be log transformed.** They will be adjusted for age, gender and BMI, and residuals will be compared between each group of homozygous individuals at each locus by Student t tests. Since these polymorphisms may influence glycemic traits by affecting BMI, both BMI-adjusted and unadjusted analyses will be reported. Secondary analyses will include exploration of genetic models (dominant, recessive or additive), by including heterozygous individuals and performing ANOVA across the three genotypic groups, with subsequent Bonferroni adjustment for multiple comparisons. The role of self-reported ethnicity will be evaluated with an interaction term; analyses will also be repeated within each self-reported ethnic group, and in the aggregate of groups where minor allele frequencies are comparable. As these experiments involve validation of previous hypotheses, nominal *P* values below 0.05 will be considered statistically significant.

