***VI.3. Power calculations***

**Our power calculations suggest that we will need to enroll ~750 subjects.** Based on our own multi-ethnic data, we have estimated a minor allele frequency of 0.32 for the risk T allele at rs7903146 *TCF7L2* and 0.35 for the risk K allele at *KCNJ11* E23K. Assuming Hardy-Weinberg equilibrium, the proportion of subjects carrying the risk homozygous genotype at either locus will be ~10% and ~12% respectively. With the difference in insulinogenic index between CC and TT homozygotes at rs7903146 *TCF7L2* documented by Saxena *et al.,* (see Section C.3 above), 750 subjects should provide >80% power to detect the same difference at a one-sided alpha of 0.05. Similarly, assuming that the difference in insulin sensitivity after one year of metformin treatment by E23K genotype is also detectable in the acute setting, 750 subjects provide >90% power at the same one-sided alpha of 0.05 (73% for a two-sided test). With regard to the sulfonylurea challenge, this sample size has >99% power to detect a 10% difference in trough glucose between genotypic groups at a one-sided alpha of 0.05, and 94% power to detect a 20% difference in peak insulin at a one-sided alpha of 0.05.

While these power calculations apply to a study population of a single ethnic group, expanding our study to include a multi-ethnic population would require enrollment of ~1,000 subjects.

1. **Risks and DIscomforts**

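### If several biological relatives from one Joslin family enrol, the planned independent-sample genotype tests understate their standard errors, probably by a small amount.

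*Protocol*

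**What the plan says.** **Recruitment.** Protocol III.1 lists several sources, with the Partners practices as the main target. For the Joslin site it adds: "At the Joslin Diabetes Center, family members of the diabetic patients will also be recruited". It gives no number, no share of the sample and no cap per family.

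**Eligibility and enrolment.** The only family-related criterion in III.2 concerns suspected monogenic diabetes: "Onset of diabetes before age 25, with autosomal transmission of diabetes across three generations". It does not bar a relative of someone already enrolled. The enrolment section (Subject Enrollment) sets no limit per family either.

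**Analysis.** In VI.2, after adjustment for age, gender and BMI, "residuals will be compared between each group of homozygous individuals at each locus by Student t tests". Secondary analyses explore genetic models "by including heterozygous individuals and performing ANOVA across the three genotypic groups". The criterion is that nominal P "values below 0.05 will be considered statistically significant". The section has no family term, clustered error, kinship adjustment or rule of one subject per family.

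**Sample size.** VI.3 states: "Our power calculations suggest that we will need to enroll ~750 subjects". The genotype group sizes follow from Hardy-Weinberg proportions, with no allowance for relatedness.

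**The concern.** A Student t test and a one-way ANOVA take their standard errors from the spread between subjects, on the assumption that no subject tells us anything about another. Relatives break this assumption in a way that matters particularly for a genetic study. In most trials relatives would share only the outcome. Here they also share the grouping variable, because siblings tend to fall into the same genotype group. Two positively correlated members on the same side of the contrast carry less information than two unrelated people, and the test does not know it. Adjusting for age, gender and BMI does not remove what siblings share in the remaining trait.

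The direction is therefore known: whenever the residual trait correlation is positive, the test is anti-conservative. At stake are P values slightly too small at the stated 0.05 threshold and an effective sample slightly smaller than the number enrolled.

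**Working it through.** **The plan's own figure.** VI.3 claims "750 subjects should provide >80% power to detect the same difference at a one-sided alpha of 0.05" for *TCF7L2*, from "a minor allele frequency of 0.32 for the risk T allele at rs7903146".
- TT: 0.32² = 0.1024, so 750 × 0.1024 = 77 subjects. CC: 0.68² = 0.4624, so 750 × 0.4624 = 347.
- Insulinogenic index from I.3.c: 0.61 (SD 0.71) in TT, 1.00 (SD 1.84) in CC; difference 0.39.
- With unpooled variances, one-sided 0.05, normal approximation, power is 92.0%, which meets the claim. With the pooled SD of 1.69 that a Student t test uses, it is 57.2%; that is a separate matter from this point.

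Either way the calculation counts 750 independent subjects.

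**Effect of relatives.** For a genotype contrast the variance inflation is approximately

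VIF = 1 + share × (m − 1) × r_g × r_y

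where share is the fraction of the sample in families with m enrolled members, r_g is the genotype correlation (0.5 for full siblings) and r_y is the correlation of the adjusted trait. The true standard error is √VIF times the reported one. The actual two-sided error is 2 × [1 − Φ(1.96/√VIF)]. Only r_g is fixed, by Mendelian transmission. The documents give none of share, m or r_y, so all three are assumed.

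| Assumed setting | VIF | √VIF | Error by formula | Error by simulation |
|---|---|---|---|---|
| 10% in sibling pairs, r_y 0.3 | 1 + 0.1×1×0.5×0.3 = 1.015 | 1.007 | 5.2% | 5.2% |
| 20% in sibling pairs, r_y 0.3 | 1 + 0.2×1×0.5×0.3 = 1.030 | 1.015 | 5.3% | 5.2% |
| 20% in trios, r_y 0.5 | 1 + 0.2×2×0.5×0.5 = 1.100 | 1.049 | 6.2% | 6.2% |
| 30% in sibships of four, r_y 0.3 | 1 + 0.3×3×0.5×0.3 = 1.135 | 1.065 | 6.6% | 6.5% |
| 30% in sibships of four, r_y 0.5 | 1 + 0.3×3×0.5×0.5 = 1.225 | 1.107 | 7.7% | 7.5% |

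The simulation ran the planned homozygote t test under the null, 20,000 runs per setting. Its Monte Carlo standard error near 5% is √(0.05 × 0.95/20,000) = 0.15 percentage points. The pair settings are therefore barely distinguishable from 5.0%, while the trio and sibship settings are clearly above it.

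**Power.** With 25% of 750 subjects in sibling pairs and r_y 0.5, VIF = 1 + 0.25 × 1 × 0.5 × 0.5 = 1.0625, so the effective sample is 750/1.0625 = 706. A one-sided power of 80% becomes about 77.9%.

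**The case against.** The strongest reply is that the harm may never occur. It needs at least two biological relatives of one family in the study. The protocol speaks of relatives of Joslin patients, and index patients already on diabetes medication are excluded by III.2. One relative per patient would then add no dependence, and a spouse is not a biological relative. The text mentions no sibling pairs or larger sets. This stands, and it is why the point is conditional.

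The second reply is about size. Joslin relatives get one sentence among sources that III.1 puts at about 1,547 + 1,500 + 500 + 100 + 200 + 1,004 = 4,851 people (overlapping or ineligible people not removed), for 750 to 1,000 places. A 30% share in sibships of four is extreme against that background. A residual sibling correlation of 0.5 is also high: under additive inheritance with no shared environment it would mean complete heritability. This stands too.

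The third reply is that relatedness may be handled in an analysis plan or genotype quality-control plan not shown here. This has some force, since naming a t test does not forbid restricting it to unrelated subjects. It does not dispose of the point: VI.2 itself names independent-sample tests, III.1 itself opens the family route, and the family link has to be captured at enrolment.

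A reader might infer more than the documents support:
- That the error is inflated for certain. It is not; it depends on who enrols.
- That an ethnic stratum in VI.2 could consist mostly of families, with errors of 8-10%. Such a stratum would behave that way, but nothing in the protocol links any ethnic group to Joslin families.
- That confidence intervals will be too short. VI.2 plans P values and names no intervals.
- That testing many variants makes it worse. The inflation applies to each test and does not grow with the number of loci.

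**Conclusion.** The point holds in conditional form and is minor. The recruitment text allows several biological relatives per family, the named tests assume independence, and nothing in the protocol reconciles the two. If such relatives enrol and their adjusted traits are positively correlated, standard errors are too small and 0.05 is exceeded. Under moderate assumptions the excess is a few tenths of a percentage point; it reaches 1.5 to 2.5 points only under the largest family share and family size considered. All these sizes rest on assumed values of family share, family size and trait correlation. If at most one biological relative per family enters, there is no effect.

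**What to change.** At enrolment, ask each subject whether a biological relative is taking part, and store a coded family identifier. Section V.7 links coded data only within a subject, so the family link would be hard to recover later.

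In VI.2, keep the same genotype contrasts and covariates, but compute them with family-clustered standard errors or a family random effect. Alternatively, state that one biological relative per family is analysed, with the choice made by a rule that uses neither genotype nor outcome.

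The cost is one recruitment question and a sentence in VI.2. Standard errors become slightly wider where relatives are present, or slightly fewer subjects are analysed under the one-per-family option. With no related subjects, the one-per-family rule leaves the planned analysis unchanged.

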Subjects will then have a 20G intravenous catheter placed, and baseline (time 0) serum insulin, metabolomic profiling, C peptide and glucose will be obtained. In addition, a comprehensive metabolic panel and an extra 20 cc tube of whole blood for DNA extraction will also be drawn. They will then receive a single oral dose of glipizide 5 mg, and simultaneous insulin and glucose will be obtained at 30, 60, 90, 120, 180 and 240 minutes. Additionally, metabolomic profiling samples will be drawn at 60 and 120 minutes. Routine glucose measurements (for subject safety) will also be obtained every half an hour from intravenous blood. The frequency of blood glucose measurements will increase to every 5 minutes for an asymptomatic glucose <50 mg/dl. If the subject develops symptoms of hypoglycemia (diaphoresis, lightheadedness, confusion, anxiety, new onset of hunger or tiredness) another glucose measurement will be obtained: 1. If glucose > 50 mg/dl, glucose measurements will increase to every 10 minutes. If subject no longer feels symptoms of hypoglycemia, the nurse may return to routine checks after 3 documented rising or stable blood sugars. 2. If any glucose measurement is <50 mg/dl (with symptoms) or 45 mg/dl (without symptoms) or if nurses detect symptoms such as confusion, blurred vision and slurred speech, regardless of glucose measurements, the challenge will be aborted and the patient will be given juice and a glucotab, and advised to break his/her fast immediately. If the subject cannot swallow, 1 amp of D50 will be administered by IV. At the conclusion of the sulfonylurea challenge, every subject will be fed a provided meal rich in carbohydrate content. Any subject with persistent symptoms of hypoglycemia after the full meal will have another glucose measurement; persons with a glucose <80 mg/dl will be monitored for another 3 hours at the clinical research center, or longer if deemed necessary for their safety by the PI.

Before discharge, the patient will receive three 500 mg metformin pills to take home with the appropriate instructions. If subject suffered symptoms of hypoglycemia, the nurse will provide them with an educational pamphlet on monitoring blood sugar as well as a snack to eat at home. Days 1-6 will constitute the washout period for the single administered dose of glipizide (~12 half-lives by a conservative estimation).

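### Genotype-directed call-back can tie genotype to recruitment source, and the homozygote comparison in VI.2 has no term for source

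*Protocol*

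**What the plan says.** **Recruitment (Protocol III.1).** "Our main target for recruitment will be the local Partners Network practices". The section also lists PCOS, metabolic-syndrome and gestational-diabetes cohorts, a former consortium of non-diabetic subjects, relatives of diabetic patients and, if needed, advertising. None of these selects on genotype. III.1 then adds "queries within an institutional biorepository containing samples adequate for genotyping and demographic information", giving as the reason that the study tests specific variants. Those who have "given consent for genotype-directed call back into future research studies will be contacted first by mail", then by phone. No genotype, number, ratio or matching rule is given.

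**Eligibility (III.2).** Two tiers of diabetes risk are preferred, the first including diet-treated type 2 diabetes, and "Otherwise healthy subjects may also be candidates for the study".

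**Analysis (VI.2).** The endpoints are "adjusted for age, gender and BMI, and residuals will be compared between each group of homozygous individuals at each locus by Student t tests". On ethnicity, "The role of self-reported ethnicity will be evaluated with an interaction term", with repeat analyses within ethnic groups. Neither recruitment source nor risk tier appears.

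**Genotype proportions.** VI.3 sizes the study on Hardy-Weinberg shares of risk homozygotes. V.8.b tests Hardy-Weinberg equilibrium within ethnic group, not by source.

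**The concern.** A genotype comparison is credible largely because genotype has nothing to do with how people came into the study. That holds for the clinic, cohort and advertising routes. It fails if one route picks people by the genotype under test, because one homozygote group then contains a larger share of that route than the other.

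The wide entry criteria make this matter. Glycemic status bears directly on the VI.1 primary endpoints: trough glucose, peak insulin, the HOMA-based sensitivity index and the insulinogenic index. If call-back subjects differ from other recruits in glycemic status beyond what age, gender and BMI explain, part of the TT-versus-CC (or KK-versus-EE) contrast is a contrast of sources. It could create a genotype effect or hide one.

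**Working it through.** **1. Reproduce the plan's own figure.** VI.3 gives minor allele frequencies of 0.32 (*TCF7L2*) and 0.35 (*KCNJ11*). Under Hardy-Weinberg, 0.32² = 0.1024 and 0.35² = 0.1225, which agree with the stated ~10% and ~12%. At N = 750, TT = 76.8 and CC = 0.68² × 750 = 0.4624 × 750 = 346.8.

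**2. What selective call-back does to the groups.** Let a share *f* of the 750 come by call-back.
- TT only, *f* = 10%: the other routes give 675 × 0.1024 = 69.1 TT and 675 × 0.4624 = 312.1 CC. Adding 75 call-backs makes TT 144.1. Call-backs are 75/144.1 = 52% of TT and 0% of CC.
- TT only, *f* = 5%: 37.5/110.5 = 34% of TT and 0% of CC.
- Equal TT and CC, *f* = 10%: 37.5/106.6 = 35% of TT and 37.5/349.6 = 11% of CC.
- Not selected on genotype: the shares are equal and there is no bias.

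**3. Bias and type I error.** Bias = (q_T − q_C) × δ. Here q_T and q_C are the call-back shares of TT and CC, and δ is the source difference in SD units left after the age, gender and BMI adjustment. Type I error comes from the normal approximation with noncentrality bias / √(1/n_T + 1/n_C), two-sided at 0.05. The documents state neither *f* nor δ. Both are assumed: *f* = 5–20%, δ = 0.2–0.5 SD.

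Worked case, TT only, *f* = 10%, δ = 0.3: bias = 0.520 × 0.3 = 0.156 SD; standard error = √(1/144.1 + 1/312.1) = 0.101; noncentrality 1.55; type I error 0.34.

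| Call-back | Bias (SD), full range | Type I error, full range | At *f* = 10%, δ = 0.3 |
|---|---|---|---|
| TT only | 0.07–0.35 | 0.095–0.97 | 0.16 SD, 0.34 |
| Equal TT and CC | 0.03–0.17 | 0.058–0.39 | 0.07 SD, 0.10 |
| Not genotype-selected | 0 | 0.05 | 0 SD, 0.05 |

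The sign follows the sign of δ, which is unknown.

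**4. Side effect on the Hardy-Weinberg check.** TT-only call-back at *f* = 10% gives TT/CT/CC counts of 144.1/293.8/312.1 and an allele frequency of 0.388. The expected counts are 112.9/356.2/280.9, and chi-square is about 23 (about 6.9 at *f* = 5%). A sound assay could then look like a genotyping failure.

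**5. What a source term does (*f* = 10%, unit SD).** With source fitted alongside genotype, the contrast is made within source, and the bias term drops out if no other source-by-genotype imbalance exists.
- TT-only call-back: the 75 call-backs have no same-source comparator. The standard error becomes √(1/69.1 + 1/312.1) = 0.133, against 0.101 unadjusted.
- Equal call-back: the within-source information is 1/(1/69.1 + 1/312.1) = 56.6 plus 1/(1/37.5 + 1/37.5) = 18.75. The standard error is 1/√75.3 = 0.115, against 0.111 unadjusted, and 0.126 if all 750 came by the other routes.

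So equal call-back with a source term removes the source bias and still gains precision.

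**The case against.** **Selection is not spelled out.** III.1 names no genotype or ratio, and the aims extend to newly discovered variants singly or in aggregate, so call-back need not target TT or KK. This stands as a limit on size. It does not answer the point: genotype-directed is the protocol's own term, the stated reason for the route is the variants under test, and nothing requires the opposite homozygotes to be called.

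**A different risk profile is not documented.** The biorepository is institutional, may overlap with the main patient pool, and its volunteers meet the same entry criteria. This stands. δ could be small, and its sign is unknown. Any figure in mg/dl would need assumed diabetes shares that no section supports.

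**Equal call-back would not cure it.** Correct: CC is about 4.5 times as common as TT (46.2% against 10.2%), so equal numbers still leave 35% against 11%. The source term is therefore the essential part of the fix.

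**The statistical analysis plan may deal with this.** It is not shown, so the lack of a sensitivity analysis is not itself a fault. VI.2 does, however, state its adjustment set, and source is not in it.

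**A stronger reading: staff know the genotype.** A reader might infer that those running the challenge know the genotype of called-back subjects, and that this could matter because "if nurses detect symptoms such as confusion, blurred vision and slurred speech, regardless of glucose measurements, the challenge will be aborted" (V.2). The documents do not say so. Study DNA is drawn on Day 1, samples carry coded identifiers, glucose and insulin are laboratory measurements, and other stopping triggers in V.2 are numeric. The coding is a confidentiality measure, and masking of call-back genotype is not stated. That supports one clarifying sentence and no more.

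**Conclusion.** The point holds conditionally. The protocol adds a genotype-directed route to routes that ignore genotype, admits a wide glycemic range, and fixes a primary comparison with no term for source. If call-back is selective and call-back subjects differ from the rest after the age, gender and BMI adjustment, the homozygote contrast is biased and the stated analysis does not remove it.

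Size and direction cannot be computed from the documents. The assumed ranges (call-back share 5–20%, residual source difference 0.2–0.5 SD) show only that a modest programme could matter: at a 5% share of TT-only call-back, type I error is already 0.095 to 0.34. With unselective call-back or no residual source difference, the bias is nil. The documents do not support saying that the genotype comparison is already compromised, that risk homozygotes alone will be called, or that biorepository volunteers are healthier.

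Confidence is medium. The correction is cheap and is best made before call-back subjects are enrolled.

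**What to change.** **VI.2 (essential).** Add recruitment source (call-back or other) as a factor in the homozygote comparison, fitted in the same model as genotype. Putting it only in the step that forms the residuals would absorb part of a true genotype effect when the two are correlated. Report a sensitivity analysis that leaves out call-back subjects.

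**V.8.b.** Test Hardy-Weinberg equilibrium within ethnic group without the call-back subjects.

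**III.1.** State that call-back at a locus invites both homozygote groups, so that a within-source comparison exists, and that the contact list reaches recruiters and clinic staff without genotype. Matching on several further factors is not needed.

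**Cost.** A source flag for each subject, one model term, one extra analysis and a short paragraph in III.1. Some call-back places go to the common genotype, and call-back subjects without a same-source comparator add little to the adjusted contrast. No clinical procedure changes.
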